#### Economic analyses

This economic evaluation will involve both a cost-effectiveness analysis (CEA) and a cost-utility analysis (CUA). Incremental cost-effectiveness ratios will be calculated by dividing the difference in total costs between conditions by the difference in average effect size. Because we calculate costs over a period of six months, correction for inflation is not necessary. Missing data on follow-up measurements will be imputed using multiple imputation. Bias-corrected and accelerated bootstrapping with 5000 replications will be used to calculate 95% confidence intervals around the mean difference in total costs between the treatment groups. Bootstrapping will also be used to estimate the uncertainty surrounding the ICERs which will be graphically presented on cost-effectiveness planes. Cost-effectiveness acceptability curves and net monetary benefits will also be calculated. Cost-effectiveness acceptability curves show the probability that collaborative care is cost effective in comparison with usual care for a range of different ceiling ratios thereby showing decision uncertainty. Sensitivity analyses will be carried out to ascertain the robustness of the findings under different scenarios, e.g. under varying values of key-variables.

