### Randomization

Randomization into two groups (experimental group and comparison group) takes place after assessment. Before randomization participants are stratified on the basis of two factors (sex: male/female and relationship: spouse/other). As a method for randomization block randomization with variable sizes is used. The allocation schedule is made with a computerized random number generator by an independent researcher and is unknown to the investigators of this study.

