#### Outcome measures in the RCT

For an overview of the instruments see Table
1.

**Table 1 T1:** Overview of instruments (measures)

	**Pre-test**			**Post-tests**		
	**Intake**	**T = 1**	**T = 2**	**T = 3**	**T = 4**	**T = 5**
Outcome measures in the RCT						
-* Depressive symptoms: CES-D*	X		X	X	X	X
- *Anxiety symptoms: HADS-A*	X		X	X	X	X
- *Role overload: SPPIC*		X	X	X	X	X
- *Caregiver perceived stress: RMBPC*		X		X	X	X
Confounders/Modifying variables						
- *Perceived control: Mastery Scale*		X		X	X	X
- *Sense of competence: SSCQ*		X		X	X	X
- *Behavioral problems: RMBPC*		X		X	X	X
- *Demographic variables*	X					
- *Diagnosis/Duration of symptoms*	X					
- *Functional status of person with dementia: IQCODE*	X					
Outcome measures in the CEA						
- *Quality of life: EQ-5D+C*		X		X	X	X
- *Health care utilization: TIC-P*		X		X	X	X
- *Time spent on caregiving*	X			X	X	X

*CES-D* Centre for Epidemiological Studies Depression scale.

*EQ-5D+C* EuroQol 5 Dimensions plus Cognition.

*HADS-A* Hospital Anxiety and Depression Scale, Anxiety subscale.

*IQCODE* Informant Questionnaire on Cognitive Decline in the Elderly.

*RMBPC* Revised Memory and Behavioral Problem Checklist.

*SPPIC* Self Perceived Pressure from Informal Care scale.

*SSCQ* Short Sense of Competence Questionnaire.

*TIC-P* iMTA Questionnaires on Costs Associated with Psychiatric Illness.

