### Statistical analysis

All analyses in the RCT-study will be conducted according to the intention to treat principle. Missing data on follow-up measurements will be imputed using regression imputation. To examine differences between the outcomes for experimental and comparison group, paired t-tests will be conducted and estimates of effect sizes will be calculated. By using multiple regression analyses, we can correct for possible confounders. With a ‘generalized estimated equations’ (GEE) analysis the research question regarding the maintenance of the effectiveness of the intervention will be answered. In addition, profiles of caregivers who respond best to the intervention will be described by means of a multiple regression analysis which also contains modifying variables (modifier analysis). All analyses will be conducted using SPSS for Windows, version 19.

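### The incremental cost is planned as a bootstrapped mean difference with no covariate named, although baseline care use, caregiving hours and the strata are collected; adjustment would narrow the interval to the extent that baseline predicts cost

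*Protocol article*

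**What the plan says.** All references are to the protocol article.

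- **Cost estimator (Economic analyses).** The BCa bootstrap "will be used to calculate 95% confidence intervals around the mean difference in total costs between the treatment groups". For the ratio, "Incremental cost-effectiveness ratios will be calculated by dividing the difference in total costs between conditions by the difference in average effect size". Neither sentence mentions a covariate. The same section specifies multiple imputation, cost-effectiveness planes, acceptability curves, net monetary benefit and scenario-type sensitivity analyses. Baseline adjustment is not listed among them.
- **Horizon (Economic analyses).** "Because we calculate costs over a period of six months, correction for inflation is not necessary".
- **Baseline data (Table 1).** "Health care utilization: TIC-P" is marked at T = 1 and again at T = 3, 4 and 5. "Time spent on caregiving" is marked at intake and again at T = 3, 4 and 5. The EQ-5D+C has a T = 1 value and the CES-D an intake value.
- **Strata (Randomization).** "Before randomization participants are stratified on the basis of two factors (sex: male/female and relationship: spouse/other".
- **Adjustment elsewhere (Statistical analysis).** "By using multiple regression analyses, we can correct for possible confounders". This sentence stands in the section on the RCT analyses, which also uses a different imputation method (regression imputation) from the economic section.

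**The concern.** Total costs here cover the person with dementia and the caregiver, include institutional admissions, and are to be seen from a societal perspective with caregiving time collected as an economic measure. Such costs vary widely between families, and part of the variation is already present at entry: whether the person with dementia lives in a care facility, whether the caregiver lives with them, and how many hours of care are being given. It is plausible that these differences persist over six months.

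An unadjusted difference leaves all of that predictable variation in the confidence interval, and from there in the plane, the acceptability curve and net benefit. The sample size is set on depressive symptoms alone and the article gives no precision target for costs, so research question 4 must be answered with whatever precision that sample yields. Baseline values that are collected anyway could improve it.

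**Working it through.** **1. The plan's own figure.** The only sample-size calculation is for the CES-D (Sample size section): d = 0.50, two-sided alpha 0.05, power 0.80.

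n per arm = 2 × (1.96 + 0.84)² / 0.50² = 62.8, so 63. This agrees with the article (power at 63 is 0.801 by the normal formula and 0.795 by the t test). For dropout, 126 / 0.75 = 168, which the planned minimum of 175 covers. No SD, correlation or target is given for costs.

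**2. Formula for adjustment.** Let r be the correlation between the baseline covariates taken together and six-month total cost. In units of the cost SD, with n per arm:

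- unadjusted variance of the difference = 2/n
- adjusted variance ≈ (2/n)(1 − r²)
- ratio of interval widths = √(1 − r²)
- equivalent sample-size factor = 1/(1 − r²)

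**3. Numbers.** r is an assumption and is varied. Unadjusted half-width at 63 per arm = 1.96 × √(2/63) = 0.349 SD.

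| Assumed r | Width ratio | Interval narrower by | Half-width, 63 per arm (SD) | Sample-size factor |
|---|---|---|---|---|
| 0.1 | 0.995 | 0.5% | 0.347 | 1.01 |
| 0.3 | 0.954 | 4.6% | 0.333 | 1.10 |
| 0.5 | 0.866 | 13.4% | 0.302 | 1.33 |
| 0.7 | 0.714 | 28.6% | 0.249 | 1.96 |

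The width ratio does not depend on n. If all 175 recruits enter through multiple imputation (about 87 per arm), the unadjusted half-width would be at best 1.96 × √(2/87) = 0.297 SD, and the percentages stay the same.

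**4. Price of the covariates.** The formula ignores the estimation of four coefficients. For normally distributed covariates this inflates the variance by about 4/(126 − 4 − 3) = 0.034, or roughly 1.7% in width. At r = 0.1 the net gain is therefore nil or slightly negative; at 0.3 and above a gain remains.

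**5. Skewed costs.** In a simulation with lognormal costs, one baseline covariate, 63 per arm, no true difference and 4000 trials per setting, the ratio of standard errors (adjusted to unadjusted) was 0.97, 0.92 and 0.79 at average raw-scale correlations of 0.22, 0.40 and 0.61. The formula gives √(1 − 0.22²) = 0.98, √(1 − 0.40²) = 0.92 and √(1 − 0.61²) = 0.79. Both estimators were centred on the true value within simulation error. The gain survives skewness, and neither estimator is biased.

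**6. Chance imbalance.** The unadjusted variance 2/n splits into (2/n)r², which enters through chance baseline differences, and (2/n)(1 − r²), which does not. Adjustment removes the first part. For example, a baseline difference of 1.96 standard errors (0.349 SD) moves the unadjusted cost difference by 0.5 × 0.349 = 0.17 SD at r = 0.5. This is the same variance as in step 3, not an additional harm.

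**The case against.** The strongest reply is that the article is silent on covariates and does not exclude them. It never calls the difference unadjusted, a BCa bootstrap can be applied to a regression-adjusted difference, and a condensed article commonly leaves a covariate set to the full plan. This stands in part: a fuller document might already contain the adjustment. But the section is not a bare outline. It fixes the estimand, the bootstrap type, the number of replications, the imputation and the outputs. Adjustment is mentioned only in the separate section on the RCT analyses. An unadjusted difference is the plain reading of what is stated.

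The second reply is that such an analysis is legitimate in a randomised trial. That stands fully. A reader might infer that the economic result is biased because chance imbalance flows into the cost difference. The documents do not support this: randomisation makes the difference unbiased, and its interval already allows for chance imbalance. For sex and relationship, stratified blocks have largely removed the imbalance anyway, so most of any gain must come from baseline costs and hours.

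The third reply is that the size is unknown. This also stands. Caregiving hours refer to a single past week and may predict six-month cost only weakly.

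Finally, adjusting costs alone would pair an adjusted cost with a differently treated effect, and the regression has to fit with the planned multiple imputation. Both points are right and shape the fix.

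**Conclusion.** The point holds as a recommendation on efficiency. As stated, the incremental cost uses none of the baseline cost information or strata that the trial collects, and it is less precise than it could be to the extent that these predict six-month cost. Under assumed r of 0.1, 0.3, 0.5 and 0.7, the interval would be about 0.5%, 5%, 13% and 29% narrower, before the small allowance for estimating the covariate coefficients. The low end is negligible and the high end is substantial; the article does not say where this trial lies. The range also assumes that T = 1 values are obtained before allocation, which fits the statement that randomisation follows assessment.

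Two stronger conclusions are not supported. The planned analysis is neither invalid nor in contradiction with another section. Nor can one say that the cost comparison loses a given amount of power: the effect size of 0.50 was set for depressive symptoms, and no powered test of costs is planned.

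**What to change.** Amend the Economic analyses section as follows.

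1. Within each imputed data set, and in each bootstrap sample drawn within arm, regress six-month total cost on arm, baseline TIC-P cost, baseline caregiving hours, sex and relationship (spouse/other). The arm coefficient is the incremental cost.
2. In the same resample, estimate the incremental effect adjusted for its own baseline value (intake CES-D for the cost-effectiveness analysis, T = 1 EQ-5D+C utility for the cost-utility analysis) and for the two strata.
3. Use this pair of estimates for the confidence interval, the cost-effectiveness plane, the acceptability curve and net monetary benefit, and state how results are combined over imputations.
4. Report the unadjusted difference as a sensitivity analysis.

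If a fuller plan already specifies the adjustment, one sentence saying so is enough. Either way, the choice should be fixed before costs are compared by arm, so that it cannot depend on the imbalance observed.

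The cost is a few sentences and two regressions inside a loop that is already planned, with no new data and no additional participants. The small downside is that the main estimate becomes model-adjusted and the analysis takes slightly more work.

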## Discussion

This study assesses the effectiveness and cost-effectiveness of an internet intervention for family caregivers of people with dementia. In the context of the fast growing number of people with dementia in years to come, there is an urgent need to develop cost-effective approaches that meet the needs of people with dementia and their family caregivers across the course of the illness. Some family caregiver may apply for help in the beginning of the course of the illness, others may use the intervention in a later stage. The potential effect of the internet intervention may act immediately or help people to keep on caring and prevent them from developing (more) health problems.

The RCT-study is conducted in the practical setting of a health provider who is specialized in dementia care and offers case management and a variety of support strategies for persons with dementia and family caregivers. Because internet delivered intervention is highly structured and leaves little room for the therapist to adapt it, in practice the structure remains intact without major adaptation
[35]. Important advantage of such a pragmatic study is that results of the study have a high level of generalizibility.

As is the case with internet therapy (or research studies in this domain) in general
[36], we expect participants to be more highly educated, with a high proportion of them having a university degree. It is also rather common that clients drop out of (research into) internet therapy. In a recent review on dropout from internet-based treatment for psychological disorders an average rate of 31% was found
[37]. Evidence on any specific variables that may make an individual more likely to drop out is currently limited
[37]. In this study we expect some family caregivers to drop out for specific disease related reasons like admission to an nursing home or death of the person with dementia. All together this may have a negative effect on the generalizability.

Primary outcome measure in the RCT is severity of depressive symptoms of the family caregiver. Anxiety symptoms, feelings of burden and caregiver stress are secondary outcomes. In a review article about consensus on outcome measures for psychosocial intervention research in dementia care, some recommendations are made for use of specific measures
[38]. It is suggested that if depression is the primary intervention target, the CES-D has potential (although it requires further validation across Europe). Also the HADS is mentioned as an useful instrument. With regard to measuring feelings of burden, authors recommend the use of the Zarit Burden Interview (ZBI). This scale has been extensively used in intervention studies, however, only a few studies show significant changes on this scale. In this study we used the Self Perceived Pressure from Informal Care scale (SPPIC) which focuses on the aspect of role overload. To measure caregiver perceived stress we use the Revised Memory and Behavioral Problem Checklist (RMBPC).

In contrast to the CES-D and the HADS, both the SPPIC and RMBPC are not often used in a web-based manner. This means that scale properties like reliability may be influenced. However, research has shown that in the case of two scales measuring depression no statistically significant differences between paper and internet-based administration were found
[39]. It is recommended that format of administration should not be changed when repeated measurements are made. Main advantage of web-based administration
[40] is completeness and reliability of data (no missing values, no data entry errors). Other advantages are time flexibility for the family caregivers and low costs.

In conclusion, we expect that this study can add important information to the knowledge base on the effectiveness and cost-effectiveness of interventions to reduce psychological symptoms in informal caregivers of dementia persons with dementia. Given the steep rise in the number of people with dementia and the crucial role family caregivers play in caring for them, interventions that reach family caregivers at an early stage are essential
[41].

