##### Frequency of reported behavioral problems

The 24 items of the Revised Memory and Behavioral Problem Checklist (RMBPC)
[25] are used to make an inventory of the number of problems family caregivers encounter. Respondents have to rate from 0 to 4 the frequency of the occurrence of the specific behavior (0 = never; 1 = seldom; 2 = regularly; 3 = often; 4 = always). The total number of behaviors problems (0 – 24) will be calculated as well as the total mean score (Behavior Frequency Score). The Behavior Frequency can be subdivided into scores on Depression (9 items), Disruptive behavior (8 items) and Memory-related problems (7 items).

Other variables that may act as confounders or modifying variables will be measured. This concerns the following demographic characteristics of caregivers: sex, age, relationship (spouse, child or other), level of education and living arrangement (living together with care recipient). Relevant patients characteristics are: sex, age, duration of symptoms (as perceived by caregiver), functional status (assessed by means of a Dutch translation of a short version of the IQCODE
[29]) and living condition (independently or within care facility).

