##### Health care utilization

An adapted version of the iMTA Questionnaires on Costs Associated with Psychiatric Illness (TIC-P) will be used to measure health care utilization and productivity losses
[34]. In this study both the direct costs related to the person with dementia with dementia and the direct costs related to the situation of the family caregivers themselves are measured. Direct costs will include the number of consultations with health care providers (e.g. general practitioner, physical therapist, psychologist, medical specialist, etcetera), medication, and admissions to hospitals and other institutions. Indirect costs are defined as the productivity lost due to absenteeism from paid and unpaid work and reduced efficiency at work (presenteeism).

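### Drop-out caused by nursing-home admission or death of the person with dementia is treated only as a generalizability issue, although it would partly hide a counted cost and leave care-specific scales to be imputed after a death

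*Protocol article*

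**What the plan says.** All references are to the protocol article.

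- **Expected drop-out.** The Discussion forecasts "some family caregivers to drop out for specific disease related reasons like admission to an nursing home or death of the person with dementia". It gives no number and no split by arm. The consequence it draws, from this and the other features of the sample it lists, is "All together this may have a negative effect on the generalizability". Bias in the comparison is not mentioned.
- **Admission as a cost.** Under Health care utilization, direct costs cover the person with dementia as well as the caregiver and include "medication, and admissions to hospitals and other institutions". The perspective is societal.
- **Possible route of effect.** The Discussion says that the intervention may "help people to keep on caring and prevent them from developing (more) health problems".
- **Timing.** Costs are calculated over six months (Economic analyses). In Table 1, TIC-P and EQ-5D+C are scheduled at T=1, T=3, T=4 and T=5. T=3 is about six months after baseline, and T=4 and T=5 apply to the experimental group only.
- **Missing data.** For effects: "Missing data on follow-up measurements will be imputed using regression imputation". For the economic evaluation: "Missing data on follow-up measurements will be imputed using multiple imputation". Neither sentence has an exception.
- **Follow-up effort.** Under Measures and measurement, non-responders receive two reminders and are then telephoned by a research assistant.

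**The concern.** Loss that follows admission differs from ordinary attrition, because the reason for leaving is itself an item on the cost side of the comparison. If the course delays admission, fewer admissions in the experimental arm would be part of its economic benefit. Those who leave after admission take that information with them, since the questionnaire that would have recorded the admission is the one that is not completed. Table 1 shows no other scheduled instrument after intake that tracks where the person with dementia lives. Imputing from caregivers who stayed, without knowing who was admitted, gives the leavers the lower admission frequency of the stayers. At stake is research question 4, societal cost-effectiveness.

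A second problem needs no event rate. SPPIC asks about pressure from giving informal care. RMBPC stress asks how stressful the behaviours are that are currently occurring. After the person has died, neither has a value to be estimated, yet a rule that imputes all missing follow-up would supply one.

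**Working it through.** **The plan's own figures.** The article gives no event rates, no event-related drop-out rate and no unit costs, so no bias figure can be derived from it alone. Its sample size is not in dispute: 2 × (1.96 + 0.84)² / 0.50² = 62.7, so 63 per arm and 126 in total. Allowing for 25% loss, 126 / 0.75 = 168, and the plan recruits at least 175. A 25% loss from 175 is about 44 caregivers, with no share given for admission or death.

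**What a caregiver who leaves before T=3 still contributes.** CES-D, HADS-A and SPPIC are also measured at T=2, so an intermediate value may exist. TIC-P and EQ-5D+C are not, so there are no follow-up cost or utility data inside the horizon.

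**Cost illustration (all rates assumed).**
- p = proportion with an admission within six months: 10% comparison, 6% experimental
- r = loss without an event: 20%
- q = loss after an event: varied
- Imputation reproduces the responders' mix within each arm and does not use event status.

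Event rate among responders:

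obs(p) = p(1 − q) / [p(1 − q) + (1 − p)(1 − r)]

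At q = 50%:
- comparison: 0.05 / (0.05 + 0.72) = 6.49%
- experimental: 0.03 / (0.03 + 0.752) = 3.84%
- difference 2.66 points instead of 4, so 66% is kept

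At q = 75%:
- comparison: 0.025 / (0.025 + 0.72) = 3.36%
- experimental: 0.015 / (0.015 + 0.752) = 1.96%
- difference 1.40 points, so 35% is kept

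At q = 20%, equal to the other loss, everything is kept. At q = 100% nothing is kept.

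Share of the true difference kept under other assumed rates, with r = 20%:

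| Event rates | q = 25% | q = 50% | q = 75% | q = 100% |
|---|---|---|---|---|
| 5% v 10% | 95% | 66% | 35% | 0% |
| 10% v 15% | 95% | 69% | 37% | 0% |
| 10% v 20% | 96% | 70% | 39% | 0% |

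**In money (assumed).** With 3 months in the facility before T=3 and a monthly cost C, the true institutional cost difference at 10% v 6% is 0.04 × 3 × C = 0.12C. For C of EUR 4,000 to 6,000 that is EUR 480 to 720 per caregiver. The part lost is EUR 161 to 242 at q = 50% and EUR 312 to 468 at q = 75%.

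**CES-D.** Assume that an event shifts the score by 0.3 to 0.8 SD, with rates of 5% v 10%. The bias is the shift times the lost part of the rate difference. At q = 50% the lost part is 0.05 − 0.0331 = 0.0169, which gives 0.005 to 0.014 SD. At q = 100% it is 0.05, which gives 0.015 to 0.04 SD. The planned effect is d = 0.50.

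**The case against.** The strongest reply is that the Discussion makes a forecast about some caregivers and sets no withdrawal rule. Analysis is by intention to treat, and the reminder and telephone procedure has no exemption after an event. That stands: a reader might infer that admission or death ends participation, but nothing in the article says so.

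A reader might also infer that the costs and distress of these events are removed from the comparison altogether. The article does not support this either. Affected caregivers who respond are counted, and complete removal requires that every one of them leaves.

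Third, the predictors in the imputation models and any targeted sensitivity analyses may be set out in a full protocol or SAP that is not shown, and general economic sensitivity analyses are planned. Their absence from an article is no fault. But an SAP can use event status and dates only if they are collected, and the article, which does describe the telephone contact, does not say that they are.

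Fourth, living in a care facility is a recorded patient characteristic. This shows that such residence is anticipated and that admission need not prevent measurement. It does not show how many such caregivers are enrolled, so it cannot be claimed that the responders used for imputation would have almost no institutional costs.

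Finally, the article does not say that a scale made inapplicable by a death counts as missing. That is fair, but the imputation sentence makes no exception, so the point needs stating.

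**Conclusion.** The concern holds as a partial bias in the cost comparison and as a gap in the rule for scales that lose their meaning after a death. Under the assumed 10% v 6% and 20% other drop-out, about a third of the difference in institutional cost is lost at 50% loss after the event and about two thirds at 75%. The proportions change little across the other rates tried. They rest on loss after an event being heavier than other loss, on admission rates differing by arm, and on imputation that ignores the event. The euro amounts rest entirely on assumed inputs and cover institutional cost only. Caregiving time, which is also in the economic evaluation, may move the other way on admission.

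A reader might infer that the primary result is at risk as well. The figures do not support that: the assumed shifts give at most 0.04 SD on CES-D, and the article does not say in which direction distress moves after admission or death.

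Calling the expected drop-out a matter of generalizability alone is therefore incomplete. The remedy is cheap and reduces bias, and most of it has to happen at data collection.

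**What to change.** 1. State that leaving the course, or admission or death of the person with dementia, does not end measurement of CES-D, HADS-A, EQ-5D+C and TIC-P.
2. Have the research assistant who already telephones non-responders record whether an admission or death has occurred, and its date, even if the questionnaire is declined.
3. Use that event information in the multiple imputation of costs.
4. Do not impute SPPIC or RMBPC stress after a death, and report admissions and deaths by arm.
5. In the Discussion, name possible bias in the comparison alongside generalizability.

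The cost is one or two extra fields on an existing call and a few sentences of protocol text. The downsides are that some caregivers are contacted at a difficult time and that the cost data become more variable, because expensive admissions that would have been missed are now counted.
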